### Intervention

The EDDIE+ program is a multi-component intervention focused on improving quality of care. It aims to educate, engage and empower RAC home staff to identify early signs of deterioration in residents and proactively intervene to avoid unnecessary hospital transfers and admissions. An implementation science-based approach is embedded within the program to support system, process and staff behaviour change with the aim of enhancing the acceptability and sustainability of the program.

EDDIE+ comprises four core components that can be tailored to meet the needs of the local context. These are: staff education and training; decision support tools; diagnostic medical equipment; and implementation facilitation (Fig. 2). The program adopts a holistic approach that seeks to engage all nurses and personal care workers within the home. It is expected that improvements from each of the core elements working synergistically will lead to sustained change via key mechanisms of impact including staff empowerment, cultural change and systems change. An intervention logic model outlining important contextual factors and mechanisms of impact is included in Additional file 1.

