### Data collection methods

#### Resident demographic and clinical data

Non-identifiable individual resident data at each RAC home will be extracted from the aged care provider’s existing routinely collected datasets. These will be used to report on the demographic characteristic summaries of the cohort to inform the generalisability of our results to other settings nationally and internationally. To review for seasonality and potential confounders over time we will use historical routinely collected data for residents at enrolled RAC homes for the two-year period directly before the trial start date.

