#### Health services use and cost data

Non-identifiable individual resident data on transfer to and from EDs and admissions to hospital will be collected prospectively by the EDDIE+ facilitators based on resident care notes, with support from the project team. Data on monthly RAC home bed availability and occupancy rates will be used in calculating ED transfer and hospital admission rates.

To supplement the prospectively collected hospital transfer data, non-identifiable individual resident health service use and cost data will be retrospectively linked using state-level administrative datasets containing detailed information on ED and hospital diagnosis codes, length of stay, discharge outcomes and costs. These administrative data will be extracted using a data linkage process based on RAC home addresses for the dates of the trial period, as well as for a historical period of 2 years directly before the trial start date. Linked data will be validated against the prospectively collected ED and hospital transfer data from the enrolled RAC homes to ensure its accuracy.

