### Analysis of primary outcome: Total number of hospital bed days

The primary outcome will be analysed using a mixed-effects Gamma regression model to estimate the impact of the EDDIE+ intervention while simultaneously accounting for RAC facility-specific variations in total hospital bed days. The key covariate will be the temporal indicator for the switch from baseline phase to intervention exposure phase, and the associated regression coefficient quantifies the change in total bed days associated with the EDDIE+ intervention period across all 12 RAC facilities. A linear time covariate in months since start of trial will be included in the regression model to capture any time trends in bed days that are not directly attributed to the intervention.

The regression model will also estimate RAC facility-specific random deviations from the overall baseline phase total hospital bed days from an RAC facility to account for any underlying differences at the different sites. It is possible that these random deviations are close to zero and the model fitting procedure may not converge. If this occurs, we will leave out the random intercept component and fit a standard Gamma regression model to the data.

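### The primary model leaves out two years of pre-trial bed-day data on the same homes and gives the programme a single on/off effect, so it gives up precision if homes differ and understates an effect that builds up.

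*Protocol article*

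**What the plan says.** The section on analysis of the primary outcome fixes the model. "The primary outcome will be analysed using a mixed-effects Gamma regression model to estimate the impact of the EDDIE+ intervention", with a random deviation for each home. On the treatment effect it says: "The key covariate will be the temporal indicator for the switch from baseline phase to intervention exposure phase". On time it says: "A linear time covariate in months since start of trial will be included in the regression model". No exposure-time term and no pre-trial rate is named.

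Under resident demographic and clinical data, "we will use historical routinely collected data for residents at enrolled RAC homes for the two-year period directly before the trial start date"; the stated purpose is "To review for seasonality and potential confounders over time". Under health services use and cost data, the linked state-level extract, which includes length of stay, covers the trial dates "as well as for a historical period of 2 years directly before the trial start date". Bed days per home can therefore be derived for the historical period. Table 1 defines the primary outcome on the baseline and intervention exposure periods only, so the history lies outside the primary estimate.

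The Intervention section expects that the components "will lead to sustained change via key mechanisms of impact including staff empowerment, cultural change and systems change". The Analysis section excludes the introduction phase.

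**The concern.** Two features of the model deserve a second look.

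First, a stepped wedge that switches one home a month leaves the earliest homes with perhaps one or two baseline months. Their own level is then poorly known, and the comparison within those homes contributes little. Two years of data on the same homes would largely settle that level, yet the plan uses them only for a review of seasonality and confounders.

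Second, one on/off term assumes that the effect is complete from the first analysed month and stays constant. Change that works through staff culture and systems may well take longer. In a stepped wedge, the on/off estimate leans heavily on the months just after each switch, so a growing effect is not merely averaged: the estimate falls below the average over exposed home-months. A programme that works slowly could be reported as having little effect.

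**Working it through.** **Inputs from the protocol article.** 12 homes of 100 residents, one switching per month, 91% power, a 41% reduction and the 5% level (sample size section); 58 weeks (abstract); 24 pre-trial months (data collection sections). The target is log 0.59 = -0.528.

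**Assumptions.** Fig. 1 is not shown, and the article gives neither the dispersion nor the between-home SD. Two layouts were used: 13 months with no introduction month, and 14 months with one introduction month removed. In both, home k has k baseline months. The test is two-sided.

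**Formulae.** c is the home-month coefficient of variation (CV) and s the between-home SD on the log scale. V has c² on the diagonal plus s² between months of the same home. SE² is the intervention element of (X'V⁻¹X)⁻¹. Power = Φ(0.528/SE - 1.960).

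**The stated 91%.** It needs SE = 0.528/(1.960 + 1.341) = 0.160. The 14-month layout gives this at CV 0.72, 0.61, 0.575 and 0.55 for s = 0, 0.2, 0.3 and 0.5. The figure is attainable but cannot be independently reproduced without those inputs.

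**Adding the history.** With 24 historical months, the between-home variance left unexplained is s²(c²/24)/(s² + c²/24). For c = 0.71 and s = 0.3: c²/24 = 0.0210, so 0.09 × 0.0210/0.1110 = 0.0170, an SD of 0.13 in place of 0.30. Power at c = 0.71 with month effects:

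| s | 13 months | 14 months, one removed |
|---|---|---|
| 0 | 95.2% → 95.2% | 91.4% → 91.4% |
| 0.1 | 93.2% → 93.8% | 88.6% → 89.4% |
| 0.2 | 88.8% → 92.5% | 83% → 88% |
| 0.3 | 85% → 92% (SE 0.177 → 0.157) | 78% → 87% (SE 0.192 → 0.171) |

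If home levels drift, with correlation falling 3% per month, the 13-month gain at s = 0.3 shrinks to 84% → 87%. If CV is instead calibrated so that the plan has its stated 91% (14-month layout), history with month effects gives 95%, 97% and 98% at s = 0.2, 0.3 and 0.5, and no gain at s = 0.

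**Straight line against month effects, no history.** The SEs are identical in the 13-month layout and agree within 0.001 in the 14-month one. The estimates under build-up are also practically the same. A yearly wave of log amplitude 0.1-0.3 shifts the planned estimate by 0% (13 months) or at most 1-3% (14 months). If the historical months are entered as data under one line over 38 months, the shift rises to about 2-8%.

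**Build-up.** Let the log effect rise linearly to its full size over L analysed months. Of 78 exposed home-months, 12 are in exposure month 1, 11 in month 2, and so on down to 1 in month 12.
- L = 3: true average (12×1/3 + 11×2/3 + 55)/78 = 66.3/78 = 85%. The on/off term recovers 62-78% of the full log effect.
- L = 6: true average ((12 + 22 + 30 + 36 + 40)/6 + 28)/78 = 51.3/78 = 66%. The on/off term recovers 27-54%.

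The ranges cover s = 0 to 0.5 and both layouts at c = 0.71. As rate ratios for L = 6, the true average is 0.59^0.66 = 0.71, and the model would report 0.59^0.54 = 0.75 to 0.59^0.27 = 0.87.

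**The case against.** The strongest reply is that both sizes rest on inputs the article does not give. The power gain depends almost wholly on between-home variation, and the article itself allows that the home deviations may be close to zero, where history adds nothing. On its own unstated inputs the design already has 91% power. Build-up is inferred: the Intervention section names gradual mechanisms but gives no time course, and excluding the introduction phase removes the first part of any ramp. Additional file 3, not shown, holds sensitivity analyses. The Discussion says that secular and seasonal risks were considered in the statistical analysis plan, and outbreak-related events are handled by analyses with and without them. All of this stands and limits the claim. None of it changes the primary model as stated.

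Some stronger readings do not hold. A reader might blame the straight-line trend; the check shows that, in an even roll-out, month effects give nearly the same precision and the same understatement. A reader might say that data already in hand are being ignored; the history is still to be extracted, and the article does assign it a use. A reader might conclude that the trial is underpowered or that its effect will be understated; the first does not follow from the documents, and the second is conditional on a build-up that they do not quantify.

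**Conclusion.** The point holds in conditional form. The omitted history costs roughly 4 to 9 points of power at between-home SD 0.2 to 0.3 (CV 0.71), under 1 point at SD 0.1 and nothing at SD 0; it costs less if home levels drift over time. The on/off term is sound for a constant effect. If the effect grows after the introduction phase, the term understates even the average effect, modestly for a 3-month ramp and severely for a 6-month ramp. The figures rest on an assumed layout, dispersion and between-home SD. The choice of linear time is not itself a fault; it becomes one only if the historical months enter the model as data.

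**What to change.** 1. Add each home's log bed-day rate over the 24 pre-trial months to the primary model as a covariate, and keep the random intercept. Take bed days from the same linked source for history and trial, and state the occupancy denominator for both. If the historical months are instead entered as data, model time by month or with seasonal terms, not one line over 38 months.

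2. Unless Additional file 3 already has it, pre-specify a supporting exposure-time analysis, for example months 1-3, 4-6 and 7-12 since introduction. Report the average effect over exposed home-months beside the on/off result.

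The cost is mainly analysis wording, since the data are already planned. One practical limit applies: the linked data are to be validated against prospectively collected transfers, and no such check is described for the pre-trial years. The exposure-time analysis has a wider interval. With CV calibrated to 91% and a truly constant effect, its power is 78-85% without history (linear time) and 92-96% with history and month effects. It should therefore support the primary estimate, not replace it. Both changes should be fixed before any unscrambled result is seen; the planned scrambled-data report is a natural place to test them.

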### Setting and participants

The trial will be undertaken at 12 RAC homes in Queensland, Australia. Data will be collected from five participant groups:
RAC homes will be enrolled in the study as the main participant group. For inclusion, the RAC homes must be located in Queensland and be operated by the study partner, Bolton Clarke, a not-for-profit aged care provider. We will purposively sample from 21 eligible homes to ensure the program is implemented across a range of regional and metropolitan settings. A lower priority will be placed on homes with existing locally implemented hospital avoidance programs to minimise potential confounding with our study intervention. A lower priority will also be placed on homes with lower bed numbers to minimise the risk of underpowering the study.All nursing staff and personal care workers at each enrolled RAC home will participate in the study, with no exclusion criteria.Data on all residents at each enrolled RAC home will be collected as part of the study, with no exclusion criteria. A waiver of consent has been granted for resident data collection in recognition of the low privacy risk and negligible participant burden, as data will be de-identified and obtained indirectly from routinely collected databases and chart notes.All family members or nominated advocates of residents at each enrolled RAC home will be invited to participate in the study, with no exclusion criteria.A purposive sample of key internal and external stakeholders at each enrolled RAC home will be invited to participate in the study, with no exclusion criteria.

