### Sample size calculation

A simulation-based statistical power calculation was performed for the primary outcome of total hospital bed days. The simulations used a stepped-wedge design of 12 sites of 100 residents per site with 1 site switched from baseline phase to intervention exposure phase each month as shown in Fig. 1. The study design was estimated to have a 91% power to detect a 41% reduction in total bed days from a baseline period total hospital bed days of 346 bed days per 100 residents per year [12]. The power calculation was based on a 5% statistical significance level.

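### The convergence fallback for the primary model drops the home effect without any check that homes really do not differ

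*Protocol article*

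**What the plan says.** Protocol article, section on the analysis of the primary outcome: "The primary outcome will be analysed using a mixed-effects Gamma regression model to estimate the impact of the EDDIE+ intervention". The covariates are the switch from baseline to intervention exposure and time: "A linear time covariate in months since start of trial will be included in the regression model". Differences between homes are carried by a random intercept, the only home term listed.

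The contingency follows in two sentences: "It is possible that these random deviations are close to zero and the model fitting procedure may not converge", and then "If this occurs, we will leave out the random intercept component and fit a standard Gamma regression model to the data". The section gives no threshold for near zero and no step between the failed fit and the plain model. It names nothing to take over the role of the home term.

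Under Setting and participants, the 12 homes are sampled purposively from 21 eligible ones "to ensure the program is implemented across a range of regional and metropolitan settings". The Discussion counts it as a strength that each home supplies both baseline and intervention data, which guards against comparing unlike settings.

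**The concern.** The rule is written for homes that barely differ, but the event that sets it off is a failed fit. A failed fit yields no dependable variance estimate, so near-zero variance cannot be read from it. In practice non-convergence would stand in for absence of a home effect, and it is not evidence of that.

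The two possible situations pull in opposite directions:

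- **Variance estimated as zero, fit converged.** The mixed model's estimates coincide with those of the plain model, so dropping the term gains nothing.
- **Fit failed while homes differ.** Dropping the term does harm. Homes that cross early supply mostly intervention months and homes that cross late mostly baseline months. Without a home term, chance differences between early and late homes enter the intervention contrast. The standard error treats repeated months from one home as independent.

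At stake is the false-positive rate of the primary test on that branch, and the within-home comparison that the design was chosen for.

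**Working it through.** **Inputs from the article**
- Layout: "12 sites of 100 residents per site with 1 site switched from baseline phase to intervention exposure phase each month" (Sample size calculation).
- Baseline rate: 346 bed days per 100 residents per year, so 346 / 12 = 28.8 per home per month.
- Duration: 58 weeks (Study design), or 58 × 7 / 30.44 = 13.3 months.
- Introduction-phase data are left out (Analysis).
- "The power calculation was based on a 5% statistical significance level"; sidedness is not stated and is taken as two-sided.

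**Assumptions, because the article gives no figure**
- Gamma shape: 2 in the main runs, 1 to 4 in the range.
- Between-home SD on the log scale, σ: 0 to 0.5. A home one SD above average has exp(0.1) = 1.11, exp(0.2) = 1.22 or exp(0.3) = 1.35 times the typical bed days.
- Two layouts, since Fig. 1 is not visible: 13 months with no gap, and 14 months with one introduction month excluded.

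**The plan's own figure.** "The study design was estimated to have a 91% power to detect a 41% reduction in total bed days". A 41% reduction is a log ratio of ln(0.59) = −0.528. The 91% can be neither confirmed nor refuted without shape and home variance. It is attainable: with σ = 0 the plain model gives 92.1% (shape 2, 14 months) or 92.5% (shape 1.75, 13 months).

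**Model.** For home *i* in month *t*, bed days are Gamma with mean 28.8 · exp(uᵢ + θxᵢₜ), uᵢ ~ N(0, σ²), and θ = 0 for false positives.
- Fallback fit: log μ = α + βt + θx.
- Alternative fit: log μ = αᵢ + βt + θx, with home as a fixed effect.
- Each tests θ / SE against *t* on its residual degrees of freedom.
- A zero variance estimate is flagged when the marginal-likelihood score for σ² at zero is not positive.

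**Results** (14 months, shape 2, 10,000 trials per row, nominal 5%)

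| σ | Plain Gamma, all trials | Fixed home effects, all trials | Share with zero variance estimate | Plain, in those | Fixed, in those |
|---|---|---|---|---|---|
| 0 | 5.5% | 6.2% | 67% | 5.5% | 5.1% |
| 0.05 | 5.7% | 5.9% | 62% | 5.8% | 5.0% |
| 0.1 | 5.9% | 5.4% | 46% | 6.1% | 3.8% |
| 0.15 | 7.8% | 5.6% | 29% | 7.7% | 4.5% |
| 0.2 | 9.9% | 6.1% | 16% | 9.6% | 4.3% |
| 0.3 | 14.1% | 6.4% | 3% | 11.8% | 5.2% |
| 0.5 | 23.0% | 6.0% | 0.1% | – | – |

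Simulation error is about √(0.10 × 0.90 / 10,000) = 0.3 points for a 10% rate over all trials. It is about √(0.118 × 0.882 / 330) = 1.8 points for the 11.8%, which rests on 330 trials. A repeat of this layout gave the plain fit 5.3%, 6.3%, 9.6%, 13% and 23% at σ = 0, 0.1, 0.2, 0.3 and 0.5.

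**Range.** Over shapes 1 to 4 and both layouts, the plain fit gives 8–14% at σ = 0.2, 11–21% at 0.3 and 17–31% at 0.5.

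**Against the planned model.** In 3,000 further trials per σ, the mixed model was fitted by quadrature with a likelihood-ratio test.

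| σ | Plain | Mixed | Fixed |
|---|---|---|---|
| 0 | 5.8% | 5.2% | 5.6% |
| 0.2 | 10.5% | 6.6% | 5.8% |
| 0.3 | 14.3% | 6.3% | 5.8% |

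At σ = 0.2 and 0.3 the planned model stays fairly close to nominal, so the inflation comes from the substitution.

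**Price of fixed effects.** Power for the 41% reduction at σ = 0 (14 months, shape 2) is 92.1% for the plain fit and 70.0% with fixed home effects.

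**The case against.** The strongest reply is that the plan reserves the fallback for home deviations close to zero. There the plain fit is at 5.5–6.1%, no worse in practice than the fixed-effects fit. This stands, and it limits the point. Suppose the rule acted only in trials with a zero variance estimate. Even charging it with all the excess over 5%, the overall rate would rise by 0.16 × (9.6 − 5.0) = 0.7 points at σ = 0.2 and 0.03 × (11.8 − 5.0) = 0.2 points at σ = 0.3. The mixed model's estimates coincide with the plain ones in those trials, so even that excess is not the rule's doing. The material harm needs a fit that fails for some other reason while homes differ, and nothing in the article says how often that would be.

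Heterogeneity is plausible but not established. All homes belong to one provider, small homes and homes with existing avoidance programs get lower priority, and the outcome accounts for occupancy. The planned report on scrambled data could also expose a convergence problem before the real results are seen. Additional file 3, cited for residual checks and sensitivity analyses, is not shown.

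What remains is that the article itself fixes the rule for the primary test, without a check on the variance. With 12 homes a near-zero estimate would be weak reassurance anyway: an estimate of exactly zero occurs in 16% of trials at σ = 0.2.

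A reader might infer that the primary analysis ignores clustering, or that the trial's false-positive rate is the 10% to 23% shown for σ of 0.2 to 0.5. The documents do not support either. The primary model has a home term, those rates apply the plain fit to every simulated trial, and no home SD is stated.

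**Conclusion.** The concern holds in a limited form. The fallback lets a numerical failure decide that homes do not differ and sets no check on that. It is close to harmless in the situation it was written for. If it is used while homes differ by an SD of 0.2 to 0.3, it roughly doubles or nearly triples the nominal error (9.9 / 5 = 2.0; 14.1 / 5 = 2.8).

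These sizes rest on an assumed Gamma shape of 2, assumed home SDs and an assumed layout with one excluded month. The direction is the same at every shape and layout tried. Because the chance of reaching the harmful branch is unknown, the severity is moderate. The point is no ground for distrusting a primary result from a mixed model that converged.

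**What to change.** Replace the fallback sentence with an ordered rule:

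1. If the mixed Gamma model does not converge, refit it with other optimisers or starting values.
2. Report a converged fit as it stands, including one with an estimated home variance of zero.
3. If no fit converges, keep home in the Gamma model as fixed effects. Confirm the result with a permutation test over the crossover orders that the randomisation could have produced.
4. Do not take non-convergence alone as evidence of no home effect, and do not fit a model that ignores home.

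Cluster-robust standard errors on the plain fit should not be the sole substitute. With a leverage correction and 11 degrees of freedom they gave 4.8–6.4% overall, but 6–13% in trials with a zero variance estimate.

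The cost is a few sentences and a little code. The statistical price should be stated in the plan: if homes truly do not differ, step 3 lowers power to about 70%, against 91–92% for the plain model under the same assumptions. Steps 1 and 2 are there to make step 3 rare. The change should be made before the real allocation is analysed; the scrambled-data report is a natural place to try it.
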